## Abstract

**Background:**

The highest incidence of tuberculosis disease (TB) in the world is in India, accounting for 26% of all new cases globally, with approximately 48,000 among persons with HIV (PWH). Unhealthy alcohol use can worsen the health of people who have TB or HIV and those who have both TB and HIV. Behavioral interventions that target alcohol use and are integrated into TB and HIV care may lead to better outcomes. This paper describes the protocol for HATHI, **H**ybrid trial for **A**lcohol reduction among people with **T**B and **H**IV in **I**ndia, a Hybrid Type 1 effectiveness-implementation trial, that tests if a behavioral intervention integrated into TB and HIV treatment, compared to usual care, results in lower alcohol use and improved TB and HIV health outcomes among people with unhealthy alcohol use in Pune, India.

**Methods:**

HATHI is a randomized controlled trial that will recruit 450 people with unhealthy alcohol use from TB and HIV clinics in Pune, India. The aims of HATHI are to: (1) test if a four session behavioral intervention integrated into TB and HIV care results in lower alcohol use among persons with TB, HIV and TB/HIV coinfection compared to usual care as measured by phosphatidyl ethanol (PEth), an alcohol biomarker (primary outcome); (2) test if the same intervention also leads to improved TB and HIV clinical outcomes including TB and HIV medication adherence, HIV viral suppression, TB sputum/culture conversion and the composite outcome of TB treatment failure, default or death; (3) evaluate barriers and facilitators to integrating the intervention into TB and HIV care, and (4) determine the incremental costs of delivering the intervention in these clinical settings. We hypothesize that the HATHI intervention will result in lower alcohol use compared to standard of care use at 6 months among people and superior TB and HIV clinical outcomes at 12 months.

**Discussion:**

This intervention addresses unhealthy alcohol use, a known barrier to optimal TB and HIV treatment outcomes. If HATHI proves effective, insights into barriers and facilitators for integration will inform future scale-up of this behavioral alcohol intervention in TB and HIV clinical settings.

**Trial registration:**

ClinicalTrials.gov
NCT04230395 (first submission 1/18/2020, most recently update 2/17/25) and India Clinical trial Registry CTRI/2020/03/024141

## Background and Rationale

India has the highest incidence of TB in the world, accounting for 26% of all new cases globally, with 48,000 among People With HIV (PWH).(1, 2)  India also ranks third globally in absolute HIV burden, with 2.6 million PWH and 64,000 new HIV infections in 2024.(3) PWH are 14–18 times more likely to develop TB, and TB is the leading cause of death among PWH.(4) Unhealthy alcohol use encompassing heavy use, heavy episodic (binge) drinking, and alcohol use disorders (AUD),(5) triples the risk of TB in the general population, increasing susceptibility to primary infection and reactivation, and also leads to poor outcomes including decreased treatment adherence, treatment default, treatment failure, relapse, and death.(6–10)

In India, alcohol use is on the rise.(11, 12) Our prior work in India has demonstrated 1) a high prevalence of unhealthy alcohol use among patients with TB, and 2) that unhealthy alcohol use is one of the major reasons for treatment default, failure, and mortality.(9, 10, 13, 14) Among PWH, unhealthy alcohol use is associated with HIV transmission, decreased use of and adherence to ART, lower viral suppression, decreased engagement and retention in care, more rapid HIV disease progression, and mortality.(15–21)

Individual-level behavioral alcohol interventions have been associated with significantly decreased HIV viral loads and increased medication adherence among PWH.(22) Such interventions among persons with TB show promise among people with TB but data are limited.(14, 23, 24) Further, despite the high burden of unhealthy alcohol use, behavioral interventions are not commonly available in TB and HIV care settings.

Brief, two to four session alcohol interventions, consisting of Cognitive Behavioral Therapy (CBT) and Motivational Enhancement Therapy (MET) are the most widely used and empirically supported behavioral interventions to reduce unhealthy alcohol use and alcohol-related harms and most frequently culturally adapted for low and middle income county (LMIC) use.(25–30) We have developed and tested culturally relevant brief counseling interventions for unhealthy alcohol use among PWH in Vietnam,(31) and for primary care settings in India.(32, 33) Maintaining the core components of these brief alcohol interventions, we have adapted them for use in HIV and TB clinical settings in India and now seek to test its effectiveness.

### Objectives

In this manuscript, we describe the protocol for HATHI, **H**ybrid trial for **A**lcohol reduction among people with **T**B and **H**IV in **I**ndia**).** Using a two arm, parallel group randomized controlled trial (RCT) design, this Hybrid Type 1 Implementation Effectiveness study tests the effectiveness of a behavioral counseling intervention (BI) on alcohol reduction (primary), and TB and HIV clinical outcomes (secondary) compared to usual care in TB and HIV clinical settings. Our aims are as follows:

#### Aim 1:

To examine the effectiveness of BI integrated into TB and HIV care compared to usual care on alcohol use.

#### Aim 2:

To examine the effectiveness of BI integrated into TB and HIV care compared to usual care on TB and HIV treatment outcomes.

#### Aim 3:

Guided by the Reach, Effectiveness, Adoption, Implementation, Maintenance (RE-AIM) implementation framework(34, 35), and using mixed methods, to 3a) evaluate patient, provider and organizational barriers and facilitators to integrated BI in TB and HIV settings

#### Aim 4:

To measure incremental costs from health system and societal perspectives of integrated BI in TB and HIV settings.

We hypothesize that compared to usual care, BI will result in 1) lower alcohol use at six months (primary outcome), 2) decreased TB treatment default, failure or death, 3) increased TB medication adherence, 4) increased retention in TB care; and among PWH, 5) increased HIV-RNA suppression, 6) increased ART adherence, and 7) increased retention in HIV care.

### Trial Design

HATHI is an on-going Hybrid Type 1 implementation effectiveness study with individual level randomization to intervention or usual care in a 1:1 ratio. A Hybrid Type 1 design, defined by Curran and colleagues as a study that primarily tests effectiveness of a clinical intervention and secondarily gathers information on its implementation potential,(36, 37) was chosen to increase efficiency of implementation should the intervention be effective. Usual care was chosen as the control condition because BI has not been tested for PWH and people with TB in India, and therefore its effectiveness in this setting has not been established. Figure 1 depicts the overall trial design.

## Methods: Participants, Interventions and Outcomes

### Study setting

The trial and all associated procedures will take place at two sites in India: Byramjee Jeejeebhoy Government Medical College (BJGMC) which is associated with Sassoon General Hospital, a major public tertiary care center (BJGMC-SGH), and Dr. D.Y. Patil Medical College and Research Centre (DYPMC), a major private tertiary care center, both in Pune, India. BJGMC is a hub for medical research, collaborating with institutions worldwide, and is in Pune Municipal Corporation Area (pop. 6.7 million). Its 1800-bed public hospital cares for underserved populations from surrounding urban and rural communities. It houses one of India’s largest HIV public sector care centers funded by India’s National AIDS Control Organization and Maharashtra State AIDS Control Society; > 24,000 PWH have been registered since 2005, and currently > 5000 patients are on antiretroviral therapy (ART). Approximately 50 PWH are seen daily with 1–2 new patients per day. The TB/Chest Department has an outpatient clinic and a 65-bed inpatient ward where 75–100 outpatients with TB and 10–15 inpatient TB admissions are evaluated daily. There are 30–35 new TB diagnoses per month among people without HIV and 12–15 new TB cases per month among PWH. DYPMC is in the Pimpri-Chinchwad Municipal Corporation area of Pune district. It has an affiliated 1470-bed hospital that serves a population of 3+ million. Like BJGMC, DYPMC has a public HIV Integrated Counselling and Testing Centre and a linked ART clinic at Yashwantrao Chavan Memorial Hospital funded by the Indian Government. Approximately 10–15 new PWH are registered per month. The Department of Respiratory Medicine has an outpatient clinic and a 60-bed inpatient ward and 7 bed ICU. They evaluate 150 outpatients for TB monthly of which 25–30 are newly diagnosed with TB. Approximately 20–25 PWH with or without TB are seen per month. This trial will be implemented in collaboration with the Maharashtra state and local TB programs. Prior to study funding, patients, caregivers and providers were engaged to discuss how to optimally integrate alcohol screening into these clinical practices and where the intervention should be delivered, thereby informing clinic based intervention instead of home-based intervention.

### Eligibility Criteria

Inclusion Criteria:
Unhealthy alcohol use defined as Alcohol Use Disorders Identification Test (AUDIT) Score ≥ 8 in men / ≥ 6 in women;Age ≥ 18 years of age;Active TB (with or without HIV) defined as either:
a) Microbiologically confirmed TB (sputum AFB smear positive by microscopy or +GeneXpert at entry) orb) Clinical TB that is subsequently confirmed by Acid-Fast Bacilli (AFB) culture;Initiating TB therapy within 30 days of enrollment.

OR
Unhealthy alcohol use defined as AUDIT Score ≥ 8 in men / ≥ 6 in women;Age ≥ 18 years of age;HIV infection.

Exclusion Criteria:
In current treatment for unhealthy alcohol use;Unable to participate in intervention sessions either due to severity of medical illness, cognitive dysfunction or active psychosis;Pregnant (will refer directly to alcohol treatment);Household member of current study participant;TB Cohort only: Patients reported to have drug-resistant TB, multidrug-resistant TB (MDR-TB), or extrapulmonary TB (EPTB). (Note: People with HIV and EPTB are not excluded)

Eligible participants with 1) severe alcohol use disorder, determined by the Mini International Neuropsychiatric Interview (MINI) MINI DSM-V,(38) 2) a history of alcohol withdrawal, or 3) a Clinical Institute Withdrawal Assessment (CIWA)(39) score of 12 or greater, will first be evaluated by psychiatry faculty at study sites, BJGMC or DYPMC for medical clearance prior to enrollment due to risk of alcohol withdrawal.

### Interventions:

#### Usual Care (UC):

Individuals randomized to the UC arm will receive provider advice to reduce or abstain from alcohol use and referral to alcohol treatment services at the provider’s discretion. In addition to usual care, at all visits, participants will also receive vital signs as part of the study to monitor blood pressure and pulse, and the CIWA will be performed to screen for alcohol withdrawal.

All participants, irrespective of assigned study condition, will receive standard of care for TB and HIV treatment, including 4-drug TB therapy and for PWH, ART. Individuals with TB randomized to UC arm will return for their routine TB treatment visits at weeks 4 and 8 where sputum will be collected per standard of care. They will have an additional study visit at week 2, where sputum will be obtained. PWH will receive standard of care delivered by the HIV clinic which includes monthly monitoring of ART side effects, clinical assessment, TB and other opportunistic infection evaluations, counseling for psychosocial and adherence support, CD4 count every 6 months, and viral load testing every 12 months.

### Intervention

Individuals randomized to the intervention will receive UC plus the HATHI intervention. The **HATHI intervention** is a manualized behavioral intervention that integrates evidence-based components of CBT/MET for alcohol reduction. The content intervention was, systematically adapted for delivery within Indian TB and HIV clinical settings and provides a counselor script to aid consistency and quality of counselor delivery. The intervention comprises four core sessions of approximately 45 minutes each, supplemented by three booster sessions of 10–15 minutes, delivered over a three-month period (at month 3, 4 and 6) and aligned to regular treatment visits when possible. The number of boosters was selected to take advantage of monthly scheduled visit during the 6 months of TB therapy.

HATHI is designed to provide relevant alcohol and health information, enhance motivation, strengthen self-efficacy, and teach practical skills to reduce at-risk alcohol use. Sessions are delivered in a **Motivational Interviewing–informed style**, emphasizing collaboration and client autonomy while encouraging individuals to explore their own reasons for change within a supportive, nonjudgmental context. Table 1 describes session timetable and content.

### Intervention Supervision and fidelity monitoring

Co-investigators (SB and GD) will initially provide weekly supervision and then transition to monthly frequency and periodically conduct direct observation of counseling sessions to ensure protocols are followed properly. Peer supervision will occur weekly throughout the study period. All the intervention sessions will be audio recorded. Initially, the first five audio recordings of the sessions of each counselor, and later a random subset of 15% of recorded sessions will be assessed to ensure fidelity to the intervention manual.

The intervention sessions will be supervised using the Motivational Interviewing Coach Rating Scale (MI-CRS).(40, 41) The purpose of the supervision is to improve counselors’ MI skills and ensure better client outcomes. MI-CRS assesses counselor skills across 12 criteria, which include empathy, collaboration, open-ended questioning, affirmation, reflective listening, summarizing, evoking client motivations, respecting client autonomy in goal setting, and balancing the client’s agenda with a focus on target behaviors. Each criterion is scored on a scale from one to four, corresponding to skill levels: beginner (1), novice (2), intermediate (3), and advanced (4).

Fidelity monitoring: In addition, the MI-CRS will be used to measure fidelity to the motivational interviewing style in intervention delivery.(40, 41) Supervisors (SB, GD) completed six hours on online MI-CRS training (three hours per day over two days), eight hours of online MI training (four hours per day over two days), and 14 days of on-site training with the study staff at the Pune office. Reliability is checked every month by (SB and GD) co-rating 1–2 sessions for adherence to MI and BI session content.

BI session supervision updates, challenges and fidelity issues encountered during implementation will be discussed in bi-monthly calls with HH, a clinical psychologist and co-investigator. These meetings will focus on reviewing session feedback and identifying strategies for improvement.

Bi-monthly reports are shared with the principal investigators, detailing session information and ratings on the MI-CRS, along with qualitative feedback for counselors that highlights their strengths and areas for improvement. Number of intervention sessions attended and booster sessions delivered will be captured in the REDCap database.

### Criteria for discontinuing or modifying allocated interventions

The intervention will be discontinued for people who become incapacitated and unable to participate in counseling visits. We will not exclude participants who return to alcohol use or are stepped up into more intensive treatment services, since these are expected outcomes for this patient population. We will attempt to retain these patients in the protocol, and the counselor will continue efforts at re-engagement unless the participant formally withdraws from the study. In the event that a participant is excluded from the study prematurely, they will continue to receive all services provided by the TB and HIV Clinics and be referred for alcohol treatment services as needed.

### Provisions for post-trial care

Individuals requesting continued alcohol care post-trial will be referred to the substance use outpatient program at BJGMC and DYPMC.

#### Outcomes

Primary outcome (Specific Aim 1): Our primary outcome is alcohol use at six months as measured by the alcohol biomarker Phosphatidyl Ethanol (PEth).(42) PEth will be collected using dried blood spots. In the initial proposal, the primary outcome measure was based on alcohol self-report, using the Time Line Follow Back (TLFB) interview.(43, 44) At the HATHI DSMB meeting on May 30, 2024, the DSMB recommended changing to PEth due to observed under-reporting of alcohol use on the TLFB by participants compared to PEth.

Secondary alcohol outcomes: We will examine the following secondary outcomes of PEth at Month 6and 12:
PEth as a binary variable at different thresholds of alcohol use: PEth ≥ 20; ≥50; ≥ 200Total drinking days in the last 30 days measured using TLFB (count)AUDIT score (Cut off: ≥8 for men, ≥ 6 for women), and continuousComposite TLFB and PEth: Total drinking days using TLFB and PEth ≥ 20; ≥50; ≥ 200Composite AUDIT score and PEth: AUDIT ≥ 8 / ≥ 6 men/women & PEth ≥ 20; ≥50; ≥ 200

Other secondary clinical outcomes (Specific Aim 2) are described in Tables 2 and 3 and defined further in Appendix 1.

##### Implementation outcomes (Specific Aim 3)

RE-AIM dimensions (34, 35), and implementation outcomes of feasibility, acceptability, appropriateness, fidelity and sustainability(35, 47) will be quantitatively assessed through study records and surveys, and qualitatively using study team meeting/counselor supervision notes and in-depth interviews focused on perceptions (beliefs, feelings) of the intervention and barriers and facilitators to implementation. Table 4 describes these outcomes.

##### Economic evaluation (Specific Aim 4)

For economic evaluation, we will assess three types of costs: implementation process costs, per-patient service delivery costs, and patient perspective costs. Implementation cost will be defined as cumulative total programmatic cost of the HATHI intervention implementation, categorically analyzed by three phases of implementation: design, initiation, and maintenance phase.(48) HATHI intervention delivery cost will be assessed as per-patient cost, incorporating implementation costs and direct healthcare resources utilized. Patient perspective costs will be assessed as cumulative patient direct out-of-pocket and indirect costs during the participants’ TB treatment until the end of patient follow-up. For cost-effectiveness analysis, the primary outcome will be the incremental cost per alcohol-free patient at endline. Secondary outcomes include incremental cost per improvements in health-related quality of life (HRQoL) score measured using the WHO QoL-BREF(49) and/or EQ-5D.(50) Additionally, we will use the trials’ primary and secondary clinical effectiveness outcomes to estimate modeled long-term projections of health-related quality of life improvements attributable to alcohol reduction and TB treatment outcomes assessed in terms of disability adjusted life years (DALYs) averted.

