#### Health system and implementation costs:

Data on health systems costs will be collected from the perspective of India’s National TB Elimination Program, which is the institution primarily responsible for financing the TB control program. Implementation cost data will be collected using a standardized activity-based time and resource use form following the framework developed by our team(48) and interviews of our research staff, which will be matched to the periodic expenditure log. HATHI intervention costs (other than human resource – assessed using time and motion data and clinical staff pay scales) and other medical service costs (e.g., clinic visit, diagnostics, drugs, etc.) will be collected based on per-patient, service-use frequencies.

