#### Aim 4: Cost and cost-effectiveness analysis

Cost of the HATHI intervention will be assessed using activity-based costing framework and ingredients approach where resource use and cost data will be assessed based on key HATHI intervention activities. Fixed costs (e.g., HATHI implementation costs) and resources common across multiple intervention activities will be apportion to each activity based on the distribution of direct human resource time committed to each intervention activities. All costs will be assessed in both local (Indian Rupees) and study year United States (US) dollars, with capital assets and fixed costs annuitized using 3% discount rate (varied between 0 and 10% in sensitivity analyses) and relevant expected useful life years.

For patient cost analysis, we will assess the number and percentage of patients avoiding catastrophic cost due to TB as a result of the intervention relative to the control arm. Catastrophic cost will be defined as TB-related patient-incurred cumulative total costs during the observational period exceeding 20% of patients’ annual household income.(71) We will examine the association between catastrophic costs and AE (e.g., treatment failure) using univariable and multivariable analyses generating odds ratios for each variable as risk factor to the catastrophic costs. This will be assessed independently for each study arm and repeated as a combined analysis for difference in proportion of participants experiencing catastrophic costs between the two study arms.

Cost-effectiveness of the intervention will be assessed based on ‘net benefits’ or net-monetary benefits approach,(72) where we will calculate incremental health systems costs per one additional patient successfully completing TB treatment and bench mark this metric against a range of willingness to pay thresholds, starting with the India’s GPD per capital for our analytic year. We will conduct additional analyses on key effectiveness outcomes – incremental cost per participant achieving alcohol reduction and per quality adjusted life years gained – to examine the relationships in the cost-effectiveness outcomes and conclusions across different effectiveness measures.

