### Ethics and dissemination

#### Protocol amendments

Protocol amendments are reported to the local IRBs, the data monitoring committee and the sponsor. Amendments are also updated in clinical trials.gov.

The following protocol amendments have occurred during the course of this study. We obtained a supplement from the National Institute on Alcohol Abuse and Alcoholism (NIAAA) to add collection and storage of plasma, urine and stool in 2023. We obtained a second supplement from NIAAA in 2024 to add an HIV only arm. The original protocol sought to recruit 450 individuals with TB (n=300) and HIV and TB co-infection (n=150) with unhealthy alcohol use. From the time of grant inception to implementation, HIV and TB co-infection incidence declined due to effective ART. Given lower recruitment of persons with HIV and TB co-infection, we added an HIV only arm, consisting of PWH with unhealthy alcohol use, with the same overall recruitment goal of 450 people. Finally, we changed the primary outcome of the study from self-reported drinking days and heavy drinking days using the TLFB to the alcohol biomarker PEth as recommended by the DSMB on May 30, 2024, due to underreporting alcohol by self-report.

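### Aim 4 names two different lead cost-effectiveness measures, and the one in the analysis section does not apply to the HIV-only stratum, with no restriction stated

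*Protocol article*

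**What the plan says.** All references are to the protocol article.

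- **Outcomes, Economic evaluation (Specific Aim 4).** The lead measure is fixed: "For cost-effectiveness analysis, the primary outcome will be the incremental cost per alcohol-free patient at endline". Next comes: "Secondary outcomes include incremental cost per improvements in health-related quality of life (HRQoL) score". Long-term modelled benefit is to be "assessed in terms of disability adjusted life years (DALYs) averted". Cost per TB treatment completed is not listed.
- **Statistical method, Aim 4: Cost and cost-effectiveness analysis.** Cost-effectiveness is to be judged by net monetary benefit, for which "we will calculate incremental health systems costs per one additional patient successfully completing TB treatment". This figure is set against a range of willingness-to-pay thresholds that begins at GDP per capita. Then: "We will conduct additional analyses on key effectiveness outcomes", namely "incremental cost per participant achieving alcohol reduction and per quality adjusted life years gained".
- **Protocol amendments.** In 2024 "we added an HIV only arm, consisting of PWH with unhealthy alcohol use", with the recruitment goal left at 450. HIV without TB is a separate route in under Eligibility Criteria, and HIV only is one of the three randomization strata.
- **Table 3.** A footnote marks the TB outcomes block as applying to TB and TB/HIV participants.
- **Health system and implementation costs.** The perspective for these data is that of the "National TB Elimination Program, which is the institution primarily responsible for financing the TB control program".

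**The concern.** An economic aim should have one lead measure, fixed in advance. Here one section gives that place to alcohol abstinence and the other gives it to TB treatment completion. An intervention can do well on one and poorly on the other. With both on record, the headline could be settled after the results are known, and either choice could be defended from the text.

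The second problem follows from the amendment. TB completion was a possible outcome for everyone under the original design (300 with TB and 150 with TB and HIV). It is not one for participants who have HIV alone. If they entered the calculation they would contribute intervention cost and could contribute no benefit. The Aim 4 analysis text does not say how they are handled.

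**Working it through.** **1. The two sections side by side.**

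| Item | Outcomes section | Analysis section |
|---|---|---|
| Lead measure | Cost per alcohol-free patient, labelled primary | Health-system cost per extra TB treatment completed, used for net benefit and thresholds |
| TB completion | Not listed | Lead |
| Alcohol measure | Alcohol-free, at endline | Alcohol reduction, an additional analysis |
| Generic health measure | HRQoL score improvement; modelled DALYs averted | QALYs gained, an additional analysis |

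The lead measure differs, the alcohol criterion differs (being alcohol-free is not the same as having reduced), and the generic health unit differs. Both statements stand in the same article, so condensing a longer document does not account for the conflict.

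**2. Who can have the TB outcome.** Participants in the TB-only and TB/HIV strata can complete TB treatment; those in the HIV-only stratum cannot. The Costing measures section describes the comparison as the intervention package against usual care, without limiting it to participants with TB.

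**3. What pooling would do.** The document gives no figure to reproduce, so this is a conditional calculation. Let *s* be the HIV-only share of the 450, *g* the gain in completion among participants with TB, and *c*_TB and *c*_HIV the incremental cost per person in participants with TB and in HIV-only participants.

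- Restricted to participants with TB: cost per extra completion = *c*_TB / *g*.
- All 450 pooled: [(1 − *s*)*c*_TB + *s* *c*_HIV] / [(1 − *s*)*g*].
- Ratio of pooled to restricted = 1 + [*s*/(1 − *s*)] × (*c*_HIV/*c*_TB).
- With equal cost per person this becomes 1/(1 − *s*).

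The shares below are assumptions, because the HIV-only number is not stated:

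| Assumed HIV-only share | Number of 450 | Factor, equal cost | Factor, HIV-only cost half of TB cost | Factor, HIV-only cost not counted |
|---|---|---|---|---|
| 20% | 90 | 1/0.80 = 1.25 | 1 + 0.25 × 0.5 = 1.125 | 1 |
| One third | 150 | 1/(2/3) = 1.5 | 1 + 0.5 × 0.5 = 1.25 | 1 |
| 50% | 225 | 1/0.50 = 2.0 | 1 + 1 × 0.5 = 1.5 | 1 |

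The inflation therefore depends on the share, on the cost ratio, and on whether HIV-only costs are counted at all.

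**4. The payer.** The health-system cost data name only the TB programme. The Study setting section describes HIV care as financed through the national and state AIDS control bodies. The health-system perspective as written does not say how HIV services are costed.

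**The case against.** The strongest reply has four parts.

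- **Only the outcomes section uses the word primary.** The analysis section describes a method and promises several measures, so all of them would be reported. It is true that no second primary is declared. But the analysis section rests net benefit and the thresholds on TB completion and calls the alcohol measure additional, which reverses the stated order. Reporting everything does not settle which result leads.
- **The natural reading is that TB completion is assessed in people with TB.** The Table 3 footnote points that way, and the Aim 2 analysis text says analyses are stratified by disease cohort. This has real weight. A reader might infer that the TB measure cannot be defined, or that it is biased against the intervention by 1.25 to 2.0. The documents do not support either: the measure can be computed in the TB-only and TB/HIV strata, and nowhere is it said that all 450 are pooled. However, the stratification sentence sits under Aim 2 and treats the subgroup results as exploratory, so it does not fix who enters the Aim 4 calculation.
- **Costs are not taken from the TB programme alone.** A reader might infer this from the health-system cost section. It would be wrong: Aim 4 names a societal perspective as well, and patients' direct and indirect costs are collected. What stands is narrower: the health-system component names only the TB programme.
- **GDP per capita is the start of a range of thresholds, and cost per QALY is also planned.** This stands, so the choice of threshold is not part of this point.

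**Conclusion.** The conflict between the two sections is an error in the text as written and rests on no assumption. The missing restriction is also a matter of record: the lead measure of the analysis section does not apply to one of the three randomization strata, and the Aim 4 text does not say so.

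The numerical consequence is conditional. Inflation by 1/(1 − share) requires pooling all 450, equal incremental cost per person, and a share the document does not give. If the analysis is confined to participants with TB, the factor is 1. The factors show why the restriction should be written down; they are not evidence of bias in the plan.

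The point is confined to Aim 4. The PEth primary analysis, the sample size and the Aim 2 clinical comparisons do not depend on it.

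**What to change.** 1. Name the same single primary cost-effectiveness measure in the outcomes section and the analysis section. Cost per alcohol-free patient is preferable: it matches the trial's main question, is defined for every randomized participant, and can use PEth, which Table 3 already schedules at baseline and months 3, 6 and 12. Use the same wording and the same visit in both places, so that alcohol-free is not exchanged for alcohol reduction.
2. Report cost per TB treatment completed as secondary, with both costs and outcomes restricted to the TB-only and TB/HIV strata.
3. State whether QALYs gained, DALYs averted or both are intended, in the same terms in both sections.
4. Use one common health-system perspective covering HIV as well as TB services for all participants. Costing HIV-only participants from a separate payer's viewpoint would mix perspectives within one comparison.

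The cost is rewording plus modest unit-cost work for HIV services. No new participant data are needed for the primary measure.
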